#### ActivOnline intervention

Participants randomized to the active intervention group will be given individualized access to the ActivOnline program (www.activonline.com.au) and encouraged to use this for the 12-week intervention period, to track their physical activity, set goals, and self-monitor progress. This will be in addition to usual care.

ActivOnline uses principles of motivational interviewing and cognitive behavioural strategies, with the aim of increasing opportunity and motivation for physical activity participation. It provides a secure portal for recording and reviewing physical activity and exercise participation details. ActivOnline is a mobile platform accessible from any internet browser across a variety of devices including tablets and smartphones. When logging into ActivOnline participants will be prompted to set weekly exercise and physical activity goals, as well as to record details of their physical activity or exercise sessions including total time and step count. To support recording of daily step count participants may use their own activity tracker (e.g. Fitbit) or mobile telephone. A pedometer (Yamax digiwalker SW500, Yamasa Tokei Keiki Co., Ltd., Tokyo, Japan) will be provided to participants on request. Data entered into ActivOnline are displayed in numerical and graphical form to allow visualization of progress over time (see Fig. 1). Participants can choose the frequency of use of ActivOnline, as data can be entered retrospectively. If no activity has been logged for three days, a standardized alert message will be issued by the ActivOnline program and emailed to the participant. Participants in the intervention group will also be able to communicate with research clinicians directly via the messaging system contained within ActivOnline about the trial or their clinical status, should they require. The number and nature of contacts via the messaging system will be recorded.

**Fig. 1 Fig1:**
[figure not shown]
ActivOnline. **a**: ActivOnline website homepage; **b**-**d**: ActivOnline data entry portal – data entry screen (**b**); real time graphical display of data (**c**); goal setting (**d**). The image depicted in (**a**) is legally sourced royalty free stock photo from Adobe Stock

### Outcome measures

Demographic details of age, gender, body mass index (BMI) and lung function will be collected at baseline, prior to hospital discharge. Details pertaining to CF genotype, age at diagnosis and status for pancreatic insufficiency will be obtained from the medical record. Frequency of access to the ActivOnline program and number of exercise sessions recorded will be extracted from ActivOnline.

Participants will undertake assessment of clinical outcome measures at baseline, end intervention and after 3 months follow-up (Fig. 2). The following measures will be recorded:

**Fig. 2 Fig2:**
[figure not shown]
Participant schedule. MVPA = moderate-vigorous physical activity; MST-25 = Modified shuttle test (25 levels); CFQR = Cystic Fibrosis quality of life questionnaire – revised; HADS = Hospital anxiety and depression scale; CES-D = Centre for epidemiological studies depression scale; HAES = Habitual activity estimation scale; PSQI = Pittsburgh Sleep Quality Index; FEV_1_ = Forced expiratory volume in one second

#### Primary outcome

The primary outcome will be time spent in moderate-vigorous physical activity (MVPA) as measured objectively using accelerometry. The intensity of physical activity will be monitored using a wrist-worn accelerometer provided to participants for seven days (Actigraph Link; Actigraph LLC, Pensacola, FL 32502 USA). This triaxial accelerometer is validated for the assessment of free-living activity and is a recommended device for the objective assessment of physical activity in individuals with CF [22]. The a priori definition for activity monitoring data to be included in the final analysis is a minimum of three days [23], for ≥10 h of valid wear time in each day [4]. Average time (minutes) per day spent in MVPA will be reported.

Accelerometers will be initialized (sampling rate 100 Hz) and downloaded using the ActiLife software (v6.10.4; Acti-Graph, Pensacola, Fl, USA). Wear-time will be established using ActiLife parameters such that a period of at least 90 min of consecutive activity counts of zero, with a spike threshold of two minutes and 100 counts per minute, will define non-wear time [24]. Pre-specified cut-points will be used to determine time spent in at least moderate intensity activity, with activity intensity thresholds determined by participant age [25, 26].

#### Secondary outcomes

Self-reported physical activity participation will also be assessed using the Habitual Activity Estimation Scale (HAES), a validated subjective measure of physical activity participation in young people with CF [27]. Two measures of physical activity participation will allow for comparison between patient perception of activity intensity and objectively measured data.Aerobic fitness will be assessed using the Modified Shuttle Test (25 level version; MST-25) [28], an extension of a field test of aerobic capacity which is a reliable and valid measure of exercise capacity in adults and children with CF [29–31]. The MST-25 is a symptom-limited estimated assessment of peak aerobic capacity with distance covered the outcome of interest. It requires participants to walk, or run as necessary, around two markers over a 10-m course in time with a pre-recorded audio signal. Each level of the test lasts for one minute, with the speed increasing by 0.61 km/hr each minute. Participants cease the test when they feel they are no longer able to continue or when they fail to meet the course marker on two consecutive shuttles [29].Assessment of the reasons underlying participants decision to engage, or not engage, in physical exercise will be undertaken using the Behavioural Regulation in Exercise Questionnaire (BREQ-2) [32]. The BREQ-2 has been used in young people [33] and adults [34] with a variety of chronic medical and psychological conditions.Spirometry measures of forced expiratory volume in one second (FEV_1_) and forced vital capacity (FVC) will be reported. Spirometry measures will be conducted according to American Thoracic Society/ European Respiratory Society (ATS/ERS) standard procedures [35].Health-related quality of life (HRQoL) will be assessed using the revised edition of the Cystic Fibrosis Questionnaire (CFQ-R) [36]. The CFQ-R is a valid and reliable tool that provides a disease-specific measure of HRQoL [36].Anxiety and depression will be evaluated using the Hospital Anxiety and Depression Scale (HADS) [37] and the Center for Epidemiologic Studies -Depression (CES-D) scale [38]. These scales have been used in establishing the prevalence of anxiety and depression in young people and adults with CF [39].As exercise can positively impact both sleep and health outcomes, participants will complete the Pittsburgh Sleep Quality Index (PSQI) [40] self-report measure of sleep quality. The PSQI has been validated widely, and previously used in children and young adults with CF [41].Healthcare utilization will be documented from the medical record. Time to next hospital admission and the number of hospital days up to 12 months following completion of the intervention period will be reported.

### Analysis

#### Sample size

To detect a difference of 20-min per day in MVPA participation between ActivOnline and control groups following the intervention period, a total of 56 participants will be required. This sample size was based on physical activity participation measured post hospitalisation in our population of young adults with CF [4] and assumes a standard deviation of 26 [4] with a power of 80% and a significance level of *p* < 0.05. It was planned to randomize a total of 75 participants to allow for 25% attrition. Over the first 18 months of recruitment there was higher than anticipated attrition for the primary outcome. It was decided to extend recruitment beyond the initial target of 75 to account for this attrition. The original trial registration incorrectly stated a different number of participants (incorrect total 150). This was due to an error in interpreting the sample size calculation. The correct number of participants required (total for both groups combined) is *n* = 56, with *n* = 19 to allow for 25% attrition, giving a correct total sample size of *n* = 75. In our original registration we had incorrectly assumed that *n* = 56 were required in each group.

#### Analysis

Continuous variables will be analysed by fitting linear mixed models, controlling for recruitment centre and baseline values as required. The proportion of participants who achieve age recommended physical activity will be compared between groups using a chi-squared test. Time to hospital admission will be evaluated using Kaplan-Meier curves and Cox proportional hazards modeling. All data will be analysed by intention-to-treat. Alpha will be set at 0.05.

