### Randomisation

Participants will be randomly allocated (1:1) to ‘usual care’ or the ‘ActivOnline’ intervention. A computer-generated, block randomization scheme will be used with stratification for 1) site of recruitment – to allow for differences in local treatment practices including those related to usual prescription of exercise, and 2) whether or not the participant is enrolled in fulltime schooling (primary or secondary versus not in fulltime schooling) as the time of transition from secondary school to university or the workforce is a known time for decline in physical activity participation [18].

Sequence generation will be performed by an individual who is independent of the research team and randomization will occur using an online database. The randomization sequence will be concealed from investigators. Participants will be allocated to groups after completion of one week of physical activity monitoring immediately following discharge from hospital. Participants will not be blind to the intervention, however all outcomes will be measured by an independent assessor blind to group allocation. The flow of participants through the study will be reported according to the recommendations of the Consolidated Standard of Reporting Trials (CONSORT) [19].

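### The plain chi-squared test of guideline achievement ignores schooling and baseline activity, so it can be conservative and lose some power

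*Protocol article*

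**What the plan says.** Three statements in the protocol article bear on this.

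- **Binary endpoint (Analysis).** "The proportion of participants who achieve age recommended physical activity will be compared between groups using a chi-squared test". No stratification or covariate is attached to the test.
- **Continuous endpoints (Analysis).** "Continuous variables will be analysed by fitting linear mixed models, controlling for recruitment centre and baseline values as required". Adjustment is therefore stated for continuous variables only.
- **Allocation (Randomisation).** "A computer-generated, block randomization scheme will be used with stratification for 1) site of recruitment", with full-time schooling (yes or no) as the second factor. The reason given for schooling is that "the time of transition from secondary school to university or the workforce is a known time for decline in physical activity participation".

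Eligibility runs from 12 to 35 years, so the sample spans school pupils and adults. The same Analysis section adds: "Alpha will be set at 0.05". The article gives no recommended-activity thresholds, achievement rates, schooling split or block size. It states no sample size or power for the proportion, which is also absent from its Secondary outcomes section.

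**The concern.** The design balances the arms on a factor that the protocol itself expects to predict activity. The endpoint is also indexed to age, so the pass mark may differ between school-age and adult participants. If achievement differs between the schooling groups, a pooled chi-squared test uses a variance that still contains the between-group spread which stratified allocation has largely removed from the treatment comparison. The real level then falls below the nominal 5% and power is lost.

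Baseline MVPA is a second unused source of precision. It is measured in the week after discharge, before allocation, and the plan already makes it available to the model for the continuous outcome.

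The sample is small and the Sample size section reports more attrition than expected for the primary outcome, so avoidable loss of power is worth removing. A significant MVPA result beside a non-significant achievement result could then partly reflect the choice of test.

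**Working it through.** **1. The plan's own figure.** Inputs from the Sample size section: difference 20 min/day, SD 26, power 80%, alpha 0.05 (taken as two-sided). The normal approximation gives 2 × (1.960 + 0.842)² × 26² / 20² = 26.5, so 27 per arm. With the t distribution, 27 per arm gives power 0.792 and 28 per arm gives 0.807, hence 56 in total. Then 56 / 0.75 = 74.7, so 75 randomised. The stated sizes reproduce. They concern mean MVPA, not the proportion.

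**2. Direction of the effect.** Take two equal schooling groups with achievement rates p1 and p2, and exact balance between arms. The variance that applies is W = [p1(1−p1) + p2(1−p2)] / 2. The pooled test uses V = p̄(1−p̄), and V − W = (p1−p2)²/4. With r = W/V, the real level is 2[1 − Φ(1.96/√r)].

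- 30% and 50%: W = 0.23, V = 0.24, r = 0.958, level 4.5%.
- 20% and 60%: W = 0.20, V = 0.24, r = 0.833, level 3.2%.
- 10% and 70%: W = 0.15, V = 0.24, r = 0.625, level 1.3%.

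A level of 2.5% needs 1.96/√r = 2.241, so r = 0.765. With p̄ = 0.5, (p1−p2)² = 0.235, which is a gap of about 49 points.

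**3. With block allocation.** Simulation with N = 56, half in school, blocks of 4 within 8 equal sites × schooling (block size and split assumed), and no continuity correction. Power is for a within-stratum odds ratio of 4.

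| Assumed rates | Level, chi-squared | Power, chi-squared | Power, Mantel-Haenszel |
|---|---|---|---|
| 40% / 40% | 5.0% | 70% | 70% |
| 30% / 50% | 4.6% | 67% | 69% |
| 20% / 50% | 4.2% | 61% | 66% |
| 20% / 60% | 3.6% | 55% | 63% |
| 10% / 70% | 2.0% | 29% | 49% |

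The schooling-stratified Mantel-Haenszel test stays at about 4.8 to 5.1%.

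**4. Tied to the protocol's 20 min/day and SD 26.** Control achievement is Φ((mean − threshold)/26); the treated mean is 20 higher. Means and thresholds (min/day) are assumptions. The first result in each cell has 28 per arm exactly balanced on schooling. The second has 75 randomised in blocks of 4 with 25% random loss.

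| Means, school / adult | Thresholds, school / adult | Control rates | Level, chi-squared | Power, chi-squared | Power, Mantel-Haenszel |
|---|---|---|---|---|---|
| 40 / 40 | 60 / 30 | 22% / 65% | 2.7%; 3.8% | 46%; 49% | 56%; 56% |
| 40 / 40 | 60 / 21 | 22% / 77% | 1.6%; 3.1% | 37%; 39% | 51%; 51% |
| 45 / 35 | 60 / 30 | 28% / 58% | 3.7%; 4.6% | 54%; 56% | 58%; 58% |
| 50 / 35 | 60 / 30 | 35% / 58% | 4.0%; 4.8% | 57%; 58% | 58%; 59% |

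The loss is 7 to 14 points in the first two rows (gaps of 43 and 55 points), about 2 to 4 points in the third, and 1 to 2 points in the fourth.

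**5. Baseline.** A logistic model with treatment, schooling and baseline MVPA (correlation 0.5 assumed) gave power of 61 to 70%, which was 9 to 20 points above chi-squared under blocks of 4. Its plain likelihood-ratio test had a type I error of 6 to 7%, so part of that gain is not real.

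**The case against.** The strongest reply is that a chi-squared test of a responder proportion is conventional and valid, that any error from ignoring the strata is in the safe direction, and that the related continuous outcome already has a model with baseline and centre. The proportion is not primary, is not among the listed secondary outcomes and carries no power claim. All of this stands, and it limits the point to efficiency.

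A reader might infer that the test roughly halves the real alpha. The documents do not support that. Halving needs a gap of about 49 points or more between schooling groups even under exact balance, and more under small blocks with attrition: the 43- and 55-point scenarios then give about 3.8% and 3.1%. The article states no rate from which such a gap could be derived. Its stated reason for stratifying points the other way: if activity declines after school, pupils are the more active group, which partly offsets any higher pass mark. In the scenario with school 50 and adult 35 min/day, the level is 4.8% after attrition and the power loss is 1 point.

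The full analysis plan may hold more detail. That does not remove the point, because the article names the test rather than leaving it open.

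**Conclusion.** The point holds as a minor one. The named test leaves out a stratification factor that the protocol regards as prognostic, and a baseline value that it already collects. The direction is well established: the test is conservative and less powerful than a schooling-stratified one whenever achievement differs by schooling.

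The size cannot be fixed from the documents. Under the assumed rates the level is about 2 to 5%, and the power loss runs from 1 to 2 points for a gap of about 23 points to 7 to 14 points for gaps of 43 to 55 points. With no gap there is no loss from ignoring schooling. These figures assume half the sample in school, blocks of 4 or exact balance, equal sites with no separate site effect, loss unrelated to arm or schooling, and no continuity correction. The conclusions about the primary outcome are not affected.

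**What to change.** In the Analysis section, replace the chi-squared test with one of the following:

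- a Mantel-Haenszel test and common risk difference stratified by schooling, with an exact version if cells are small; or
- a Firth (penalised) logistic model with treatment, schooling and baseline MVPA, reported as a marginal risk difference.

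The first is the simpler choice and kept its level in the simulations. The second also uses baseline; the penalised form is suggested because the plain likelihood-ratio test ran at 6 to 7%. Stratifying the test by schooling alone is sensible at this size: crossing it with eight sites makes 16 cells, or 56/16 = 3.5 evaluable participants each.

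The cost is analysis wording only. No data, visits or participants are added, and since the Trial status section says recruitment is ongoing, the change can be made before results are known.

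### A baseline-covariate model would drop randomised participants whose pre-allocation wear week is invalid; modelling baseline as a response keeps them, while extra recruitment restores precision only

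*Protocol article*

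**What the plan says.** Four statements in the protocol article bear on this point.

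- **Analysis:** continuous outcomes are analysed by linear mixed models, controlling for centre and, as required, for baseline. The section then says "All data will be analysed by intention-to-treat".
- **Primary outcome:** "The a priori definition for activity monitoring data to be included in the final analysis is a minimum of three days", each with at least 10 h of valid wear.
- **Randomisation:** "Participants will be allocated to groups after completion of one week of physical activity monitoring immediately following discharge from hospital". The trigger is completion of the week. No check of the downloaded data against the wear rule is described. Participants are not blind to allocation.
- **Sample size:** "Over the first 18 months of recruitment there was higher than anticipated attrition for the primary outcome". The planned allowance was 25%, and the stated response was to recruit beyond 75.

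**The concern.** Put together, these statements allow a participant to be randomised with a baseline week that the plan does not accept as data. If baseline MVPA then enters as a covariate, a standard fit discards that participant completely, even when the end-intervention and 3-month weeks are valid. This loss would come on top of outcome attrition that already exceeds the allowance, and it is avoidable.

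A second matter is what the extra recruitment can do. It replaces lost information. If the participants without a valid outcome differ systematically from those with one, and differently by arm, a larger sample gives a narrower interval around the same shifted estimate. Device wear could plausibly relate to illness, activity or allocation, since participants know their group.

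**Working it through.** **1. The plan's own figures.** Inputs from Sample size: "To detect a difference of 20-min per day in MVPA participation between ActivOnline and control groups following the intervention period"; "assumes a standard deviation of 26"; "with a power of 80% and a significance level of" 0.05. From Randomisation: 1:1 allocation. Two-sided testing is assumed.

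- Normal approximation: n per arm = 2 × (1.960 + 0.842)² × 26² / 20² = 26.5, so 27 (54 in total).
- Two-sample t-test: 27.5, so 28 per arm = 56 in total, with power 80.7%. This matches the plan.
- Attrition: 56 / 0.75 = 74.7, so 75. This matches too.

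**2. Cost of dropping invalid baselines.** Let q be the share of participants with a valid outcome but no valid baseline, and r the baseline–outcome correlation. Neither is in the document. In units of the unadjusted outcome variance, a participant with both weeks carries information 1/(1 − r²), and one with the outcome only carries 1. This takes the baseline mean as well estimated and the invalid baselines as unrelated to outcome.

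- Baseline as covariate: information (1 − q)/(1 − r²).
- Baseline as response: information (1 − q)/(1 − r²) + q.
- Variance ratio, covariate to response: 1 + q(1 − r²)/(1 − q).

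| q | r | Variance ratio | Standard error larger by |
|---|---|---|---|
| 0.10 | 0.4 | 1 + 0.111 × 0.84 = 1.093 | 4.6% |
| 0.10 | 0.7 | 1 + 0.111 × 0.51 = 1.057 | 2.8% |
| 0.20 | 0.4 | 1 + 0.25 × 0.84 = 1.210 | 10.0% |
| 0.20 | 0.7 | 1 + 0.25 × 0.51 = 1.128 | 6.2% |

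A numerical check with N = 94 and 35% missing at 12 weeks (both assumed) gives about 3–5% at q = 0.10 and 7–10% at q = 0.20. The exact figures move by a point or two with how the follow-up visits are modelled.

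As a pessimistic bound, remove 10% or 20% of the 56 and do not replace them. The unadjusted t-test at 50.4 and 44.8 evaluable has power 76.3% and 71.1%, against 80.7% at 56. This overstates the loss, because extended recruitment may replace these participants and baseline adjustment itself gains precision.

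**3. What extra recruitment repairs.** The missing rates below are assumed.

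| Missing | Power if recruitment stopped at 75 | N for 56 evaluable |
|---|---|---|
| 30% | 78% | 80 |
| 35% | 75% | 87 |
| 40% | 71% | 94 |
| 50% | 63% | 112 |

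More recruitment therefore does repair power.

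**4. What it does not repair.** For each arm let m be the fraction missing and g the mean of observed minus missing participants. The observed difference departs from that in all randomised by m₁g₁ − m₀g₀, which contains no N.

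- 30% missing in both arms, gap 10 min/day in both: 0.30 × 10 − 0.30 × 10 = 0.
- 30% missing in both arms, gap 10 or 20 min/day in ActivOnline only: 3 or 6 min/day.
- 40% missing in both arms, same gaps in ActivOnline only: 4 or 8 min/day, against the 20-min target.

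A simulation with no true effect, SD 26, r = 0.5 and about 33–35% missing, analysed with baseline adjustment, shows the same pattern:

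- Missing completely at random, or at random given baseline: bias about 0, type I error 4.4–5.5%.
- Missingness driven by the unobserved outcome in the ActivOnline arm only: bias 5.9–6.0 min/day at N = 76, 94, 150 and 300, with type I error 15.5%, 17.7%, 24.8% and 45.9%.

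The gaps, rates and mechanisms are assumptions chosen to show the dependence. They are not estimates for this trial.

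**The case against.** A reader might infer that the wear rule contradicts the intention-to-treat claim, that it caused the attrition above 25%, and that the result is therefore biased. The document supports none of these.

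- The wear rule says when a week of accelerometry counts as a measurement. It removes data and not participants. A likelihood-based mixed model can analyse everyone with an observed response as randomised. The Withdrawal section fits this reading: data up to withdrawal are kept unless permission is declined, and protocol violations are not grounds for withdrawal.
- The attrition statement gives no cause. Withdrawal or missed visits may explain it. It also covers only the first 18 months of a recruitment that was still open.
- Bias appears only under an assumed informative mechanism. Under missing-at-random given what is modelled, there is essentially none.
- A sample-size section naturally discusses recruitment, and this one does not claim that recruitment cures bias. The missing-data policy and sensitivity analyses commonly sit in a statistical analysis plan, which is not shown, so their absence is not a fault.

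All of that stands. It is also true that baseline adjustment is only as required, so the loss of participants is not certain, and that no invalid baseline is reported. What remains is narrower. The allocation trigger is stated without a validity check, and the most ordinary reading of the model, baseline as a covariate, loses participants that another form of the same model keeps.

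**Conclusion.** The point holds as a limited, inexpensive improvement to the primary model. If baseline MVPA is a covariate, randomised participants without a valid baseline week are lost. The standard error is then larger by about 3–5% at 10% invalid baselines and about 6–10% at 20%, for assumed correlations of 0.4 to 0.7. If every baseline is valid, this loss is nil. The share of invalid baselines is not in the document.

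Attrition above 25% is reported, and the stated remedy restores precision only. Bias from informative missingness is possible, but its size and direction cannot be judged without the rate, the causes and the split by arm. The stronger conclusion, that the intention-to-treat label is false or the estimate biased, does not follow from the text.

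**What to change.** In the Analysis section, specify the primary linear mixed model with baseline, end-intervention and 3-month MVPA all as responses, a common baseline mean across arms, separate arm effects at the two later visits, and adjustment for centre. The common mean is valid because the baseline week precedes allocation. Every randomised participant with at least one valid week then contributes, although one with only a valid baseline adds little about the treatment effect. Describe the result as an analysis of participants as randomised under missing-at-random, and report by arm how many had no valid week. In the Sample size section, say that the extended recruitment is meant to restore precision.

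The cost is a few sentences and a change in model specification, with no new data and no change to trial conduct. The change does not protect against informative missingness. Requiring a valid week before allocation, with a repeat if needed, is not part of this fix. It would move some baselines later in a design that measures immediately after discharge, so it is a trade-off and not a free gain.
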